### Study population

Study participants were recruited from six participants-identifying centres (PICs) in and around London (Supplementary Table 1). For consistency, all participants were processed at a single site: the William Harvey Clinical Research Centre, Queen Mary University of London. Hypertensive patients, who were receiving between one and four antihypertensive medications, were eligible for recruitment if they had elevated systo-diastolic BP on daytime ambulatory BP monitoring ((ABPM): daytime average SBP of ≥135 and <170 mmHg, and daytime average DBP of ≥85 and <115 mmHg) and the presence of one or more of the following conditions: obesity, type 2 diabetes, heart rate ≥70 beats per minute, metabolic syndrome, dyslipidaemia, or polycystic ovarian syndrome (see Table 1 for summary of key inclusion criteria and further details in Supplementary Table 2). Exclusion criteria included atrial fibrillation, eGFR < 45 mL/min, type 1 diabetes mellitus, poorly controlled type 2 diabetes (HbA1c > 69 mmol/mol) and/or or insulin therapy, and orthostatic hypotension (defined as a fall >20 mmHg in SBP on moving from sitting to standing). The full list of exclusion criteria can be found in Supplementary Table 3.

**Table 1 T1:** Summary of participant inclusion criteria.

Inclusion criteria
Aged ≥18 and <80 years
Taking between 1 and 4 antihypertensive medications (inclusive)
Confirmed diagnosis of hypertension
24-hour ABPM mean daytime^a^ SBP ≥ 135 mmHg and <170 mmHg and mean daytime DBP ≥85 and <115 mmHg
Moreover, participant must have **one or more** of the following associated conditions:
Obesity [Body Mass Index (BMI) > 30 kg/m^2^ or waist circumference >94 cm (men) or >80 cm (women)] NB. For participants of Southeast Asian/Chinese/Japanese origin these cut-offs are >90 cm (men) or >80 cm (women)
Type 2 diabetes-controlled or sub-optimally controlled (HbA1c ≤ 8.5% or ≤69 mmol/mol) on diet and/or medications except insulin
Heart rate (any one of the three recordings) ≥70 bpm (measurement taken after 5 min of rest in a seated position) or heart rate ≥60 bpm if taking beta-blocker medication
HbA1c ≥ 42 mmol/mol or fasting glucose (if available) ≥5.6 mmol/L **AND** either low HDL cholesterol (≤1.03 mmol/L for men and ≤1.29 mmol/L for women) or high triglycerides (≥1.7 mmol/L)
Both low HDL cholesterol (≤1.03 mmol/L for men and ≤1.29 mmol/L for women) **AND** high triglycerides (≥1.7 mmol/L)
Diagnosed or known polycystic ovarian syndrome

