### Randomisation

Eligible participants were randomised in a 2:1 ratio to the tAN and sham-tAN intervention arms, respectively, using the online randomisation tool “Sealed Envelope.” This tool employed block randomisation and a dynamic minimisation approach to ensure balanced allocation between treatment groups (38). The minimisation algorithm incorporated the following baseline factors: age (<65 or ≥65 years), sex, body mass index (BMI; <30 or ≥30 kg/m^2^), and mean daytime average SBP (<160 or ≥160 mmHg).

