### Sample size

The trial was powered for the primary endpoint (change in daytime ambulatory SBP between baseline and the end of the treatment at 12 weeks) in the active treatment arm. This was done using a paired *t*-test approach.

Using a conservative assumption of a mean change in SBP of 5.5 mmHg with a standard deviation of 11 mmHg, based on the existing data for hypertensive patients, 34 participants were required to give 80% power to detect such a change at the two-sided alpha level of 0.05. After inflation for a potential 10% drop-out and a further 10% non-compliance, we required 42 subjects in the intervention (tAN) arm.

The study also recruited participants to be randomised to the sham-tAN arm to compare changes in SBP in those undergoing treatment to consider potential Hawthorne and placebo effects. In order to collect more data regarding safety in the active treatment group, the trial recruited double the number of subjects for the active treatment than for the sham treatment—a randomisation ratio of 2:1. Therefore, the sample size for the sham-tAN treatment was 21, with a total sample size across both arms of 63 subjects.

The sample size of 63 subjects (42 tAN, 21 sham), using a 2:1 randomisation ratio, provided 80% power to detect a between-arm difference of 8.4 mmHg in daytime SBP assuming no attrition, or 9.3 mmHg assuming a 20% attrition (10% dropout plus 10% non-compliance).

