### Statistical methods

Baseline demographic and physiological characteristics will be presented separately by trial group. The main analyses of the primary and secondary endpoints will be conducted on an intention-to-treat population (all randomised participants with available data irrespective of their compliance with the device) and on a per-protocol population (all participants with treatment compliance on 80% or more days during the trial). Any participants who required a change in antihypertensive medication during the treatment period for safety/ethical reasons or otherwise will be included in the intention-to-treat analyses but not in the per-protocol analyses.

The primary endpoint, change in daytime ambulatory SBP, will be calculated for each participant by subtracting the end-of-treatment measurement (at 3 months) from the baseline measurement. The mean change in daytime SBP within each group will be presented with 95% confidence intervals (CIs) within the active treatment arm. The crude difference in the mean change in daytime SBP between treatment arms will be calculated with a 95% CI, and a two-sample *t*-test with equal variances will be used to test the null hypothesis of no difference in the change in SBP between groups.

Adjusted analyses will be conducted using linear regression, comparing change in SBP between treatment groups while adjusting for baseline daytime ABPM SBP (ANCOVA), age, sex, and BMI. The estimated adjusted difference in change in SBP will be presented, along with 95% CIs and *p*-values. The primary endpoint will also be analysed according to subgroups defined by (i) BMI at baseline (<30 kg/m^2^ vs. ≥30 kg/m^2^), (ii) diabetes status at baseline, (iii) age at baseline (<65 years vs. ≥65 years), and (iv) mean ABPM daytime SBP at baseline (<160 mmHg vs. ≥160 mmHg); for each of these four risk factors, a test for interaction will be conducted between groups. Moreover, data from the urinary antihypertensive drug screening samples collected at visits 2, 4, and 5, providing objective longitudinal data on antihypertensive medication adherence for each participant from the point of randomisation to end of treatment, will be used to adjust the analysis of the primary outcome for partial or non-compliance to medications.

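### The interaction test for baseline daytime SBP cuts at 160 mmHg, near the top of a 135 to <170 mmHg entry window; a continuous term would use the data better

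*Protocol article*

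**What the plan says.** Under Statistical methods, the article analyses the primary endpoint in four subgroups. One is "mean ABPM daytime SBP at baseline (<160 mmHg vs. ≥160 mmHg", and "for each of these four risk factors, a test for interaction will be conducted between groups". Under Study population, eligibility requires "daytime average SBP of ≥135 and <170 mmHg". Under Randomisation, the minimisation algorithm uses the same threshold: "mean daytime average SBP (<160 or ≥160 mmHg". The adjusted analysis of the primary endpoint is a linear regression "adjusting for baseline daytime ABPM SBP (ANCOVA), age, sex, and BMI", with no cut stated for baseline SBP. Under Sample size, the planning values are a "mean change in SBP of 5.5 mmHg with a standard deviation of 11 mmHg" and 42 tAN versus 21 sham participants. The article gives no baseline SBP distribution and no expected count at or above 160 mmHg, and it claims no power for the interaction tests.

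**The concern.** Baseline daytime SBP is continuous, but the stated test of effect modification reduces it to two levels. The cut is well off-centre, so the upper stratum is likely to be the smaller one, and its sham cell smaller still under 2:1 allocation. An unbalanced split in a trial of 63 gives an imprecise interaction estimate, and it ignores all variation in SBP within each stratum. At stake is what the trial can say about whether the effect depends on starting blood pressure, which could inform the larger studies named in the Introduction. A few unusual changes in the upper stratum could also be over-read.

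**Working it through.** **Inputs from the article.** SD of change 11 mmHg; 42 tAN and 21 sham; 80% power; two-sided alpha 0.05; entry 135 to <170 mmHg; cut 160 mmHg. The share p at or above 160 mmHg is not given, so it is an assumption throughout.

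**The plan's own figures reproduce.**
- Paired t-test, change 5.5, SD 11: n = 34 gives power 0.808.
- Inflation: 34/(0.9 × 0.9) = 41.98, so 42.
- Two-sample t-test: 42 versus 21 gives 8.37 mmHg (stated 8.4); 34 versus 17 gives 9.34 mmHg (stated 9.3).

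**Size of the upper stratum and information kept.** For a linear interaction, the fraction of information kept by the cut is the squared correlation between SBP and the indicator SBP ≥160. Uniform case: the stratum means are 165 and 147.5, a gap of 17.5; the variance is 35²/12 = 102.1; p = 10/35 = 0.286. Information kept = 17.5² × 0.286 × 0.714 / 102.1 = 0.61. The other rows are normal distributions truncated to the entry window.

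| Assumed baseline SBP (mean, SD before truncation) | Share ≥160 | Expected n of 63 (sham) | Information kept |
|---|---|---|---|
| 145, 8 | 3.3% | 2.1 (0.7) | 20% |
| 145, 10 | 7.3% | 4.6 (1.5) | 33% |
| 150, 8 | 10.3% | 6.5 (2.2) | 36% |
| 150, 10 | 14.9% | 9.4 (3.1) | 45% |
| 150, 15 | 21.5% | 13.5 (4.5) | 54% |
| 155, 10 | 26.6% | 16.7 (5.6) | 55% |
| Uniform | 28.6% | 18.0 (6.0) | 61% |

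These are scenarios, not bounds. A distribution packed closer to 135 mmHg gives fewer still (mean 135, SD 10 before truncation: 0.8 of 63).

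**Detectable interaction with the cut** (normal approximation, same share above the cut in both arms). SE = 11 × sqrt[(1/42 + 1/21)/(p(1−p))] = 2.94/sqrt[p(1−p)]; detectable interaction = (1.960 + 0.842) × SE.
- p = 0.286: SE 6.5, detectable 18 mmHg
- p = 0.15: SE 8.2, detectable 23 mmHg
- p = 0.10: SE 9.8, detectable 27 mmHg
- p = 0.07: SE 11.5, detectable 32 mmHg
- p = 0.50, for reference: SE 5.9, detectable 16.5 mmHg

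With 34 versus 17 participants, the 18 mmHg becomes about 20 mmHg.

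**Detectable interaction with SBP continuous.** Per 1 SD of baseline SBP: 2.802 × 11 × sqrt(1/42 + 1/21) = 8.2 mmHg. To compare like with like, multiply by the gap between stratum means in SD units, sqrt[information kept/(p(1−p))].
- p = 0.149: sqrt(0.45/0.1268) = 1.88 SD, so 8.24 × 1.88 = 15.5 mmHg, against 23 mmHg with the cut.
- p = 0.073: sqrt(0.33/0.0677) = 2.21 SD, so 8.24 × 2.21 = 18.2 mmHg, against 32 mmHg with the cut.

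**The case against.** The strongest defence is that the cut was not chosen arbitrarily. It was fixed in advance and repeats a minimisation factor, so the arms should be roughly balanced on it, and an interaction test is already the right guard against over-reading one stratum. That stands as an explanation of the cut. It does not restore the information lost: balancing an allocation needs categories, a regression term does not.

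Second, the small sample is the main cause of the weakness. Even an even split would need 16.5 mmHg, and the continuous test still needs about 15 to 18 mmHg over the same gap in the scenarios with 7 to 15% above the cut. This stands. The gain is real, but it does not make the test well powered.

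Third, the full SAP is not shown and may already contain a continuous interaction model. The point therefore concerns only the method that the article states.

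A reader might infer that only a handful of participants will lie above the cut and that half the information is lost. The article gives no baseline distribution to support either as a fact: a uniform spread puts 18 of 63 above the cut and loses 39%. Nor do the documents support a charge that p-values within strata are planned, since only interaction tests are described. Nothing has been shown against the age and BMI cuts. The Discussion's description of the trial as hypothesis-generating refers to secondary and exploratory endpoints and the sub-study, so it does not settle the role of these subgroups.

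**Conclusion.** The point holds as a minor, cheap improvement. The stated interaction test for baseline SBP uses an off-centre cut that loses roughly 40 to 80% of the information on a linear interaction. Its detectable interaction is about 18 mmHg if baseline SBP is spread uniformly and 23, 27 or 32 mmHg if 15%, 10% or 7% lie above the cut, against 8.4 mmHg for the main comparison. These figures rest on the planning SD of 11 mmHg, all 63 participants analysed, a normal approximation and assumed baseline distributions. A smaller residual SD in the ANCOVA would shrink all the detectable interactions in proportion. It would be wrong to infer that the main result is compromised: neither the two-sample comparison nor the covariate adjustment depends on this cut. The article contains no contradiction here, only a less efficient choice.

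**What to change.** Before unblinding, make the interaction test for baseline SBP a treatment-by-continuous-baseline-SBP term in the planned ANCOVA. Report the estimated treatment effect with its 95% confidence interval across the entry range, and keep the prespecified <160/≥160 split as a descriptive table with the number in each arm. The same can be done for age and BMI, where the loss has not been quantified; diabetes status stays binary. If unblinding has already taken place, report the continuous term as an added analysis and label it so.

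The cost is one model term per factor and a change of wording, with no new data. The downside is the assumption of a roughly linear interaction. The result should still be presented as exploratory.

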### Procedure

Trial participants were required to attend five visits spanning 12 weeks/84 days: visit 1 for the screening; visit 2 for baseline and randomisation at Day 0; visit 3 at Day 14; visit 4 at Day 28; and visit 5 for the end of treatment at Day 84 (see Figure 2 for Flowchart). Participants also received several telephone calls: one between days 1 and 3, one on Day 7, one at Day 56, and one at Day 112 (post-trial follow-up). Participants received text and/or email reminders at Day 42 and Day 70. The expected total duration of participation was 16 weeks. No changes in antihypertensive medications were permitted during the trial (between randomisation on Day 0/visit 2 and end of treatment on Day 84/visit 5). Table 2 summarises the assessments and data collected at each visit with a full detailed schedule provided in Supplementary Table 4.

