## Discussion

The SCRATCH-HTN trial is a double-blind, sham-controlled study evaluating the safety and acceptability of tAN using the AffeX-CT device and a novel stimulation algorithm for the first time in human subjects. The trial employs an improved protocol involving bilateral tragus stimulation. In addition to assessing safety, the study investigates the potential efficacy of tAN in reducing BP in patients with uncontrolled hypertension despite ongoing treatment. The findings are expected to pave the way for further evaluation of this innovative technology and establish it as a viable therapeutic option. Through the number of secondary and exploratory endpoints and the sub-study, the SCRATCH-HTN trial is designed to be hypothesis-generating. By examining the effects of tAN on sleep quality, exercise tolerance, heart rate variability, central BP, cardiac structure, and autonomic function, the study aims to provide mechanistic insights and data on related potential therapeutic benefits that may inform future studies. If effective, or if tAN demonstrates efficacy within the constraints of statistical power considerations, tAN could represent a transformative approach to hypertension management, fostering further research into this device and its applications in the field.

The study was carefully designed to mitigate known risks associated with device-based and non-pharmacological interventions in hypertension trials. The trial participants were required to have uncontrolled BP despite receiving medication, who were asked to avoid any changes in their medication. Although there is an increased risk of cardiovascular sequelae from uncontrolled hypertension, the trial duration was just 12 weeks, a shorter period than that which patients invariably wait between community and secondary care visits following dose escalation. Those patients at higher risk with recent complications of hypertension such as stroke, myocardial infarction, or decompensated heart failure that require strict control of BP were excluded from the trial at screening. Moreover, we carefully monitored the patients during the trial period and if their BPs were at levels that could potentially damage target organs acutely, for example, mean average office SBP > 180 mmHg or DBP > 120 mmHg, we allowed the introduction of another medication or escalation of existing antihypertensive treatment as per the current guidelines and their physician’s advice.

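### Adjusting the primary outcome for urine-measured drug adherence at Days 28 and 84 conditions on post-randomisation data; that estimate should be labelled supplementary and kept apart from the randomised effect

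*Protocol article*

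**What the plan says.** Three statements in the protocol article, Statistical methods, describe the between-arm analysis of the primary endpoint (change in daytime ambulatory SBP from baseline to 3 months):

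- **Unadjusted comparison:** "The crude difference in the mean change in daytime SBP between treatment arms will be calculated with a 95% CI", with a two-sample t-test.
- **Baseline-adjusted comparison:** linear regression "adjusting for baseline daytime ABPM SBP (ANCOVA), age, sex, and BMI".
- **Adherence adjustment:** after the subgroup analyses, the section brings in "data from the urinary antihypertensive drug screening samples collected at visits 2, 4, and 5". These, it says, "will be used to adjust the analysis of the primary outcome for partial or non-compliance to medications". The period they cover is given as "from the point of randomisation to end of treatment".

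The Procedure section dates the visits: "visit 2 for baseline and randomisation at Day 0; visit 3 at Day 14; visit 4 at Day 28". It places the last of them, visit 5, on Day 84, when treatment ends.

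The article gives no model, covariate coding or estimand for the adherence adjustment and does not say whether it is a main, sensitivity or supplementary analysis. It refers to a full statistical analysis plan in Supplementary Material 3, which is not shown.

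**The concern.** The visit 2 urine result is a baseline measurement, and adjusting for it is unobjectionable. The visit 4 and visit 5 results are not. They are taken after participants have used their allocated device, and visit 5 is also the visit at which the primary endpoint is measured.

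The article itself describes two ways in which drug intake after randomisation could depend on arm:

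- The Discussion accepts that participants might work out their allocation, and this could change how they take their tablets.
- The Discussion says that at high blood pressure "we allowed the introduction of another medication or escalation of existing antihypertensive treatment". Drug intake can therefore respond to blood pressure, which is the outcome. Statistical methods keeps such participants in the intention-to-treat analysis.

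If either happens to a different extent in the two arms, two problems follow. First, adjustment removes the part of the assignment effect that runs through drug intake, so the estimand changes. Second, adherence and blood pressure may share unmeasured causes such as motivation or side effects. Conditioning on adherence then links arm to those causes, and the coefficient need not equal the total or the direct effect.

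What is at stake is the reading of the report. Several estimates of the primary endpoint are planned, and an unlabelled adherence-adjusted one could be presented as the treatment effect. Continuous secondary endpoints are to be analysed in the same way as the primary, so the adjustment could carry over to them.

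**Working it through.** **1. Timing**

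| Urine screen | Day | Relation to randomisation |
|---|---|---|
| Visit 2 | 0 | Baseline |
| Visit 4 | 28 | After |
| Visit 5 | 84 | After; same visit as the primary endpoint |

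Two of the three measurements follow randomisation. No choice of model changes that.

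**2. Yardstick from the plan's own figures**

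The article states no figure for the adherence adjustment. For scale, its detectable between-arm difference can be reproduced. With SD 11 mmHg and 42:21, the standard error is 11 × √(1/42 + 1/21) = 2.94 mmHg. The two-sample t-test at two-sided 0.05 and 80% power then detects 8.37 mmHg, which matches the stated 8.4.

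**3. Closed form without a shared cause**

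The change is baseline minus end of treatment, so a positive value is a fall in SBP. Let d be the direct device effect, b the SBP reduction from taking the drugs, and Δ the adherence difference (tAN minus sham).

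- Effect of assignment = d + b × Δ
- Adherence-adjusted coefficient = d
- Gap (adjusted minus assignment effect) = −b × Δ

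Take d = 5.5 mmHg. The article uses this figure for the within-arm change; using it as the device effect is an assumption, and so is b = 8 mmHg.

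- Δ = 0: gap 0.
- Δ = −0.05: gap 8 × 0.05 = 0.4 mmHg.
- Δ = 0.62 − 0.79 = −0.17: assignment effect 5.5 − 1.36 = 4.14, gap 1.36 mmHg.

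**4. Simulation with a shared cause**

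The assumed model is: fall = 5.5 × arm + 8 × adherent + 5 × u + noise (SD 8). Adherence follows a probit model with an arm shift of −0.5 and a coefficient of 0, +0.7 or −0.7 on u. There are 42 and 21 participants and 3,000 replicates.

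| Shared cause | Unadjusted | Adherence-adjusted | Gap |
|---|---|---|---|
| None | 4.15 | 5.52 | 1.37 |
| +0.7 | 4.32 | 6.18 | 1.86 |
| −0.7 | 4.37 | 4.85 | 0.48 |

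Adherence is about 62% against 79% in the first row, and about 60% against 75% in the rows with a shared cause. Smaller arm shifts in the same model give smaller gaps:

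- −0.25 (about 8 points): about 0.25–0.9 mmHg
- −0.15 (about 5 points): about 0.1–0.6 mmHg
- none: no gap, with both estimates about 5.5

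**5. Direction**

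A separate large-sample regression assumes 65% adherence on sham and a drug effect of 8 mmHg. Its shared cause is a standard normal variable that moves adherence by 15 points and SBP by 4 mmHg per unit.

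| Adherence shift on tAN (points) | Effect of assignment | Adjusted, no shared cause | Adjusted, shared cause |
|---|---|---|---|
| −20 | 3.9 | 5.5 | 6.0 |
| −10 | 4.7 | 5.5 | 5.7 |
| 0 | 5.5 | 5.5 | 5.5 |
| +10 | 6.3 | 5.5 | 5.2 |
| +20 | 7.1 | 5.5 | 4.9 |

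The adjusted figure is above the assignment effect when tAN lowers adherence and below it when tAN raises it. With no direct effect at all, a shared cause and a 20-point shift, the adjusted coefficient is about +0.5 (shift −20) or −0.6 (shift +20) where the direct effect is zero.

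**The case against.** A reader might infer that the randomised comparison is being replaced. The text does not support that. The crude intention-to-treat difference and the baseline-covariate ANCOVA come first and contain no adherence term. The adherence sentence comes after the subgroup analyses and reads most naturally as an addition.

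A reader might also infer a large bias from the Introduction's figure of about 84% non-adherence in uncontrolled hypertension. That is a background prevalence and says nothing about a difference between arms, which the bias requires. The article gives reasons to expect any difference to be small. Participants, clinical team and analysts are blinded, active current is set below the perception threshold, and participants were told to keep their medication unchanged and were checked. A 17-point difference has no source in the article, and even a gap of 1.9 mmHg is less than one standard error (2.94 mmHg).

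Finally, the article names no method. Weighting or another adherence-specific approach would fit its wording as well as a regression covariate would, and the unseen analysis plan may supply a method and a label. An adherence-specific effect is a legitimate supplementary question in a phase 2a trial.

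All of this limits severity and rules out any claim about the actual size of the bias. It does not remove the point. The article states that on-trial results will be used to adjust the primary-outcome analysis, and nothing in an unseen plan can turn Day 28 and Day 84 into baseline. The Discussion does call its blinding-related work sensitivity analyses, and no such label is given here.

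**Conclusion.** The point stands in limited form and should be fixed. An estimate adjusted for visit 4 and 5 urine results is not the effect of assignment to tAN if adherence or drug intake differs by arm, and it can be too high or too low. The two other between-arm analyses are sound and remain the randomised comparisons.

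The size in this trial cannot be derived from the article. The ranges of 0.1–0.6 and 0.5–1.9 mmHg illustrate what would follow from assumed adherence differences of about 5 and about 15–17 points, an assumed 8 mmHg drug effect and assumed shared causes. They are not estimates of what will occur. If adherence does not differ by arm, the gap is zero. No sample-size figure changes.

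**What to change.** Reword the adherence sentence, and the matching text in the analysis plan if it reads the same way:

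1. In any adjusted estimate of the randomised effect, use only the visit 2 (Day 0) urine result, alongside the other baseline covariates.
2. Report visit 4 and visit 5 adherence by arm, with the between-arm difference.
3. If an analysis using on-trial adherence is kept, label it supplementary; state its estimand, method and assumptions, including no unmeasured common causes of adherence and SBP where the method needs that; and do not present it as the treatment effect.
4. Apply the same rule to the continuous secondary endpoints.

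The cost is wording only, with no new data and no change to sample size. The small downside is that on-trial adherence no longer enters the main adjusted estimate; it is still reported under items 2 and 3.
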